## **Objectives**

### Primary objective

To evaluate the ability of the intervention versus control arm to increase the probability that patients screened as having moderate-severe ( $\geq 5$ ) worst pain will experience a clinically important improvement of 30% on a 0-10 NRS 1 week later.

### Secondary objectives

1. To evaluate the ability of the intervention arm versus the control arm to:
  - i. improve mean worst and average pain severity in patients screened as having clinically significant ( $\geq 2$ ) worst pain from time of screening to 1, 2 and 4 week later by half a standard deviation (0.5 SD).
  - ii. improve patient empowerment in patients screened as having clinically significant ( $\geq 2$ ) worst pain at 1, 2 and 4 weeks post-screening by 0.5 SD on the Health Education Impact Questionnaire (heiQ) (2).
  - iii. improve the experiences of unpaid carers of participating patients at 2 and 4 weeks by 0.5 SD on the Carer Experience Scale (CES) (3).
2. To compare the mean patient quality of life (QOL) at 1, 2 and 4 weeks post-screening between the intervention and control arm.
3. To test the cost-effectiveness of the implementation package versus control arm.
4. To inform understanding of the mechanisms by which outcomes are improved to inform ongoing refinement and tailoring of the complex intervention to different service settings and patient populations in the future.

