## 5.2.3 Secondary outcomes

### 5.2.3.1 Patient pain

Secondary outcomes will relate to the potential for the intervention versus usual care arm to result in the following:

1. Increase in mean reduction for worst pain severity in patients with clinically significant ( $\geq 2$ ) and moderate-severe ( $\geq 5$ ) worst pain from screening to 1 week later by half a standard deviation (0.5 SD). A MID will be assumed to be 0.5 standard deviation (SD), which is an established rule of thumb for patient reported outcomes (50).
2. Decrease in mean scores for worst and average pain across all screenings to give a population measure of effect. As for the primary outcome, the MID will be considered to be a 0.5 SD difference between control and intervention arms.

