## 1209 **5.5 STATISTICS**

### 1210 **5.5.1 Statistical analysis**

1211 For the main analysis, linear mixed models (5) will be used to model the outcomes of interest, while  
1212 accounting for the clustering and longitudinal design. Although designed for the analysis of  
1213 continuous outcomes, we have conducted computer simulations to confirm that this approach will  
1214 work very well for the pain and other NRS scores that are measured on a ten point scale. The linear  
1215 mixed modeling framework is very flexible. For example, it will allow for testing whether treatment  
1216 effects diminish over time. It will also allow the incorporate of additional covariates of interest, for  
1217 instance patient age, gender, ethnicity and other factors related to their type of disease; and  
1218 inclusion of covariates that reflect characteristics of the study centres. Statistical analysis will be  
1219 performed using the library lme4 in the R package (58). Analyses will be repeated for all patients  
1220 and patients newly referred during the intervention arm to control for the possibility that outcomes  
1221 are influenced by care received prior to the intervention being implemented. For secondary patient  
1222 outcomes, analyses will be repeated for patients with clinically significant ( $\geq 2$ ) and moderate-severe  
1223 ( $\geq 5$ ) worst and average pain.

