### 1224 **5.5.2 Sample size and power calculations**

1225 To assess the appropriate study sample size and compute study power, we used a carefully designed  
1226 computer simulation allowing for 20% dropout by both sites and patients. Drawing on data from  
1227 1,612 consecutive patients (59), outcome data were generated to mimic pain scores we expect to see  
1228 in the presenting population. We generated data from a beta distribution (scaled 0 to 1), rescaled to  
1229 lie between 0 and 10, then rounded to integer values. We then discarded patients with scores of  $< 2$   
1230 to represent the sample of interest. We allowed centre-specific means to vary between .05 and .15 to  
1231 generate an appropriate intra-class correlation. We used a standard minimally important difference  
1232 of .5 effect size (60). To more closely represent reality, we allowed for variation in the responses of  
1233 each patient to intervention. Once a hypothetical study population had been generated, we ran a  
1234 linear mixed model that included an intervention effect as well as an intervention by time effect, as  
1235 well as a random centre effect. We repeated this whole process several hundred times and then  
1236 estimated power by computing the proportion of times that the null hypothesis would be rejected.  
1237 We did this both for the main intervention effect, as well as the intervention by time effect. Two-  
1238 sided hypothesis tests with type I errors of 0.05 were used. Assuming 82 patients per centre at 6  
1239 sites ( $N=492$ ), our study will have  $>90\%$  power to detect the main effect. The study will oversample  
1240 by 2 sites (i.e. a total of 8 sites) and 18 patients per site (i.e.  $N=100$  at each site) to allow for drop-  
1241 out.

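### The secondary pain outcome is a change from screening, but the protocol does not name the screening score as a covariate; adding it gains precision and guards against unequal starting scores at no cost

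*Protocol*

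**What the plan says.** Secondary objective 1(i), in the Trial Summary and again in section 2.2.2, covers worst and average pain in patients whose screening worst pain is 2 or more: "worst pain from time of screening to 1, 2 and 4 week later by half a standard deviation (0.5 SD". Section 5.2.3.1 item 1 defines the corresponding outcome as "Increase in mean reduction for worst pain severity in patients with clinically significant" or moderate-severe worst pain, at one week. Both are changes from the screening score, and eligibility rests on screening worst pain.

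Section 5.2.3.1 item 2 is a separate outcome on the screening scores themselves: "Decrease in mean scores for worst and average pain across all screenings to give a population measure of effect".

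On the analysis, section 5.5.1 says "For the main analysis, linear mixed models (5) will be used to model the outcomes of interest, while" accounting for clustering and the longitudinal design. It adds that further covariates can be included and gives examples: "instance patient age, gender, ethnicity and other factors related to their type of disease; and" characteristics of the centres. The screening score is not among the examples. It is not listed under the descriptive and control variables in 5.2.5. The power simulation in 5.5.2 used a "linear mixed model that included an intervention effect as well as an intervention by time effect, as" well as a random centre effect, again without a screening-score term.

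Table 1 shows the pain NRS collected at screening and at weeks 1, 2 and 4. The inclusion criteria require each patient to be able to complete both the worst and the average item.

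**The concern.** Patients enter because their screening score was high enough, and that score is then subtracted from the follow-up score. Some fall towards the usual level is therefore expected in both arms with no treatment effect. The fall cancels in the comparison only if the arms start level.

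Level starting scores are not assured here. Sections 3.5 and 3.6 make the arms different patients, seen at different times, at no more than eight centres, and assigned by the arm their centre is in when they first present. Section 3.7 says that health professionals and data collectors are not blinded.

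Two things are at stake. A plain change score fixes the coefficient of the screening score at one instead of estimating it, which adds noise. It also carries part of any chance or case-mix difference in screening score into the estimated effect. A covariate that is already collected for every patient deals with both.

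**Working it through.** **The protocol's own figure.** Section 5.5.2 states more than 90% power with 6 centres of 82 (492 patients), a 0.5 SD effect and two-sided 0.05. A simple comparison of 246 with 246 gives 99.98%. The Hussey-Hughes stepped-wedge formula (6 centres, 7 periods, 82/7 patients per centre-period, ICC assumed between 0.001 and 0.20) gives 92.7% to 98.2%. The statement is consistent with these. It cannot be rerun exactly, because the beta parameters, ICC and step layout are not given. A rough simulation gave at least 99.7% without period effects and 86.5% to 88.8% with free period effects. The point below does not depend on this figure.

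**Inputs that the protocol does not give (assumed).** Integer scores from 0 to 10, mean 3.5 and SD 2.8 before selection; correlation between screening and follow-up of 0.3, 0.5 or 0.7; selection at 2 or more, or at 5 or more.

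**Precision.** Let b be the slope of follow-up on screening among selected patients, and s the SD of their screening scores.

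Var(change) - Var(adjusted) = s² × (1 - b)²

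This is positive unless b = 1. Simulation of the selected scores gives:

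| Group | Correlation | b | Adjusted / change variance | Extra patients equivalent (1/ratio - 1) |
|---|---|---|---|---|
| 2 or more | 0.3 | 0.28 | 0.74 | 35% |
| 2 or more | 0.5 | 0.47 | 0.82 | 22% |
| 2 or more | 0.7 | 0.68 | 0.90 | 11% |
| 5 or more | 0.3 | 0.29 | 0.86 | 16% |
| 5 or more | 0.5 | 0.49 | 0.91 | 10% |
| 5 or more | 0.7 | 0.69 | 0.95 | 5% |

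These are patient-level variances. Without selection and with equal SDs the ratio would be (1 + correlation)/2, that is 0.65, 0.75 or 0.85. Selection reduces the gain. Using the unselected ratios, a 0.5 SD effect (SD of a single score) and an assumed ICC of 0.05, Hussey-Hughes power for change against adjusted is 82.5% against 94.8% at correlation 0.3, 92.8% against 97.7% at 0.5, and 99.3% against 99.8% at 0.7. These power gaps are therefore on the generous side.

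**Chance or case-mix difference in screening score.** If both arms regress to the same usual level:

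Apparent effect in change = (1 - b) × screening difference

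For an illustrative 0.5-point difference among patients scoring 2 or more: 0.72 × 0.5 = 0.36, 0.53 × 0.5 = 0.265, 0.32 × 0.5 = 0.16 points. The 0.5 SD target in that group is about 1.0 point. The protocol gives no source for a difference of that size.

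A null simulation (correlation 0.6, 246 per arm, scores of 2 or more, no clustering) agrees:

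- Arms level: the change score is unbiased, with 4% false positives.
- 0.2 SD screening difference: the change score is off by 0.17 points, with 11% false positives.
- 0.5 SD screening difference: it is off by 0.45 points, with 65% false positives.
- The adjusted analysis stays near zero bias, with 3% to 4% false positives throughout.

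**A real shift in the screened population.** This is the situation that 5.2.3.1 item 2 looks for. Suppose that the package lowers everyone's mean by 0.5 points, at screening and follow-up alike, with no further effect after screening. Among patients scoring 2 or more the screening gap is then only about 0.25 points. The change contrast favours the package by about 0.14, 0.10 or 0.06 points. The adjusted contrast is the change contrast plus (1 - b) × 0.25:

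- 0.14 + 0.72 × 0.25 = 0.32
- 0.10 + 0.53 × 0.25 = 0.23
- 0.06 + 0.32 × 0.25 = 0.14

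Among patients scoring 5 or more the figures are about 0.23, 0.18 or 0.11 for change and 0.32, 0.24 or 0.14 adjusted. Both contrasts favour the package, and the adjusted one does so more.

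**Wording of the outcome.** If follow-up = a + d × arm + b × screening + error, then change = a + d × arm + (b - 1) × screening + error. The arm effect d is identical, so the outcome need not be redefined.

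**The case against.** The strongest reply is that nothing in the protocol says that the analysis will be unadjusted. The covariates in 5.5.1 are offered as examples, the model in 5.5.2 is the one used for power, and how a baseline value enters a secondary model is commonly left to a statistical analysis plan, which is not at hand. A change outcome is compatible with adjustment. So is a longitudinal model that treats screening as the first measurement, provided that the arms share a common screening mean; with separate means it returns the plain change contrast. All of this stands. The point is therefore that the covariate is not named, not that it has been ruled out.

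It is also fair that the outcome is secondary, that no stated figure is wrong, that the correlation is assumed, and that at a correlation of 0.7 the gain is modest.

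Two stronger readings are tempting and not supported. A reader might infer that any difference in screening score turns into a false effect. Only (1 - b) of it carries over, and it is false only when it reflects chance or case mix. A reader might also infer that, if the package lowers screening scores, a change analysis is biased against it. The population-shift calculation shows the change contrast still favouring the package in that case.

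What the reply does not remove is that the protocol defines the outcome by subtracting a score on which patients were selected, and lists candidate covariates and control variables without that score.

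**Conclusion.** The point holds as a no-cost improvement to a secondary analysis. The protocol defines the secondary pain outcome as change from screening and does not name the screening score as a covariate. If the score is left out, the loss is equivalent to about 11% to 35% more patients in the group scoring 2 or more, and about 5% to 16% in the group scoring 5 or more. A chance or case-mix imbalance would also leave (1 - b) of itself in the estimate. With level arms there is no bias. These sizes rest on the assumed score distribution and on correlations from 0.3 to 0.7.

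Adjustment is not a cure for every imbalance. If the package lowers pain in the whole screened population, the adjusted contrast includes part of that shift, so it needs to be read together with 5.2.3.1 item 2. The documents do not support saying that the planned analysis is unadjusted, or that it is biased in a known direction.

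**What to change.** In section 5.5.1, state that the linear mixed model for the secondary change-in-pain outcomes (objective 1(i) and 5.2.3.1 item 1) includes the same item's screening score as a fixed covariate: screening worst pain for worst pain, screening average pain for average pain. Where weeks 1, 2 and 4 are modelled together, add its interaction with week. Judge the adjusted arm difference against the 0.5 SD margin already chosen.

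The outcome may stay worded as change, and the items and time points in objective 1(i) and in 5.2.3.1 item 1 stay as written. Add one sentence saying that, if the package lowers pain in the whole screened population, the adjusted contrast contains part of that shift and is to be interpreted alongside 5.2.3.1 item 2.

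The cost is wording only. The screening score is already collected from every patient in the analysis, and no further data or patients are needed.

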## **Sample size**

100 patients with score 5+ on a numerical rating scale for pain at screening recruited at Week 1 for worst pain score (50 during the control arm and 50 during the intervention arm) per site, across eight sites.

## **Analysis**

163 For the main analysis, linear mixed models (5) will be used to model the outcomes of interest, while  
164 accounting for the clustering and longitudinal design. Sensitivity analyses will be used to explore  
165 the effects of the intervention for different sub-groups and to explore objective 3.  
166 The primary outcome for cost-effectiveness analysis will be the incremental cost per additional  
167 responder at the end of Week 1 (response is defined as a clinically important improvement of 30%  
168 on a 0-10 NRS 1 week post-screening for those with moderate-severe ( $\geq 5$ ) worst pain). Quality of  
169 life data collected at weeks 1, 2 and 4 will be used to conduct a modelled cost-utility analysis. As  
170 economic data may be skewed, confidence intervals will be estimated with bootstrap methods (6).  
171 Sensitivity analysis will examine the effect of assumptions and determine which cost components  
172 drive the results.  
173  
174 Thematic coding and classifying techniques will underpin the analysis of semi-structured interviews  
175 and focus groups (7).  
176  
177  
178

|     |                                                                                                                         |           |
|-----|-------------------------------------------------------------------------------------------------------------------------|-----------|
| 179 | CONTENTS                                                                                                         |           |
| 180 | TRIAL SUMMARY .....                                                                                              | 5  |
| 181 | CONTENTS .....                                                                                                   | 9  |
| 182 | LIST OF ABBREVIATIONS .....                                                                                      | 11 |
| 183 | BACKGROUND AND RATIONALE .....                                                                                   | 12 |
| 184 | 1.1 REVIEW OF THE LITERATURE.....                                                                                       | 12        |
| 185 | 1.2 WORK BY THE CURRENT TEAM.....                                                                                       | 13        |

**LIST OF ABBREVIATIONS**

|                   |                                                                                                                     |
|-------------------|---------------------------------------------------------------------------------------------------------------------|
| AKPS              | Australian Karnofsky Performance Scale                                                                              |
| CES               | Carer Experience Survey                                                                                             |
| CRF               | Case report form                                                                                                    |
| DOB               | Date of birth                                                                                                       |
| ECOG              | Eastern Cooperative Oncology Group Performance Status                                                               |
| EORTC QLQ-C15-PAL | European Organisation for the Research and Treatment of Cancer
Quality of Life Questionnaire for Palliative Care |
| EORTC QLQ-C30     | European Organisation for the Research and Treatment of Cancer
Quality of Life Questionnaire for Cancer          |
| EORTC QLQ-U       | European Organisation for the Research and Treatment of Cancer
Quality of Life Questionnaire Utility measure     |
| heiQ              | Health Education Impact Questionnaire                                                                               |
| HREC              | Hospital Research Ethics Committee                                                                                  |
| ImPaCCT           | Improving Palliative Care through Clinical Trials                                                                   |
| MBS               | Medicare Benefits Scheme                                                                                            |
| PBS               | Pharmaceutical Benefits Scheme                                                                                      |
| PISCF             | Participant information sheet and consent form                                                                      |
| NRS               | Numerical rating scale                                                                                              |
| QOL               | Quality of life                                                                                                     |

285  
286  
287

## BACKGROUND AND RATIONALE

### 1.1 Review of the literature

In 2007, 339,000 Australians – or 1.6% of the population - had been diagnosed with cancer within the last 5 years (8). As cancer treatments evolve, those who previously would have died within months are now living with cancer as a chronic condition often in addition to other co-morbidities, with a heavy burden of physical and psychological symptoms (9). Most people with advanced cancer, in particular, present with symptoms related to both cancer and its treatment (10). Symptoms also impact on informal carers, with an estimated 2.6 million Australians providing home care to someone affected by illness or disability, many of whom have cancer.

Pain is experienced by 30-75% of people with cancer and is rated as moderate-severe by 40-50% and severe by 25-30% (11). Studies show that up to 42% have inadequate analgesia (12). Undertreated pain not only reduces patient quality of life (QOL) but also increases health service use, impacts on carers and, at a societal level, reduces the ability of patients and carers to participate actively in employment and other activities. A wealth of literature highlights barriers to pain assessment and management at the levels of patients (e.g. reluctance to report pain, misconceptions regarding opioids), health professionals (e.g. lack of time and expertise) and the healthcare system (e.g. lack of coordination and timely access to analgesia) (13-18). Patients from non-English speaking backgrounds are likely to suffer especially poor levels of care because they are less able to communicate their needs and navigate the healthcare system (19). Patients in regional and rural areas may also not receive the same standard of care as those in metropolitan areas (20), despite the fact that minimum standards for pain assessment and management can be readily achieved without input from specialist services in the overwhelming majority of cases where pain is not complex. These standards include routinely screening and assessing pain, providing patients with pain self-management strategies, ensuring availability of regular and breakthrough analgesia, and offering laxatives to patients receiving opioids (21). Studies have shown that implementation of evidence-based clinical practice guidelines for pain recommending these standards can improve the processes of care and patient outcomes (22).

In Australia, pain in people with cancer has been identified as an important area for improvement by both the National Institute of Clinical Studies (NICS) and the Cancer Institute New South Wales. The recently launched Australian National Pain Strategy has six major goals including, ‘timely access to best-practice, evidence-based assessment and care’ (23). The Pain Strategy was developed in 2010 at a National Pain Summit and included input from a *Cancer Pain and Palliative Care Working Group* chaired by the current lead investigator. This Group concluded that a primary objective should be promotion of guidelines and systems to ensure adequate assessment and management of pain in people with cancer.

As well as evidence-based, pain management needs to be person-centred. The experience of pain and meaning attributed to it vary substantially between different individuals (13). People often present with comorbid health conditions and other symptoms. Their priorities and preferences also vary according to other commitments in everyday life. For example, people with cancer pain commonly seek a balance between pain and the side-effects of medication, altering dose according to their activities on a day to day basis (24). Patients can be appropriately considered experts in their own pain, both in its experience, exacerbating and ameliorating factors, and in their pain-related needs within the context of their wider lives (25). This means that the role of supportive care might be best thought of as supporting self-management by patients and carers, providing the necessary information, resources and expert advice. Unfortunately, however, patients often report that they get

‘lost in the cracks’ of the health system, and that their care is centred more around the different services they encounter than their needs.

In summary, a comprehensive, systems-based approach is needed to ensure evidence-based assessment and management of pain is implemented across settings and geographical locations for people with advanced breast and other cancers. At the same time, however, special attention is needed to ensure that systems approaches do not lose sight of individual patients.

A systematic review identified three models that have been shown to succeed at least to some degree in implementing evidence-based care for cancer pain (22): 1) institutional models, which provide policies and procedures for regular pain assessment and standardisation of pain treatment; 2) clinical pathways, which provide step-by-step guidance on optimal sequencing and timing of assessment and management; and 3) expert consultation. The reviewers concluded that a clinical pathway combined with a consultation model is currently the optimal method for supporting the most important features of pain assessment and management, namely patient education, an interdisciplinary approach and continuity of care.

A number of systematic reviews have found computerised symptom screening cancer settings to be feasible and acceptable and to contribute to improved processes of care such as doctor-patient communication and referrals (26-28). Evidence is less consistent and compelling for impacts on symptom severity or QOL, suggesting that structured interventions of the kind to be used in the current study are required to ensure screening results are used to optimally inform management.

